### 5.3 Protocol structural and functional MRI

After 12 weeks of treatment, patients will visit the neuro-imaging centre in the early morning; they will be instructed to be in a fasting state and not to inject their prandial insulin. All scans will be acquired at the same time of the day to minimise diurnal variations. Patients will be made comfortable in a supine position on the scanner table. If they are using glasses, they will receive a special pair that can be used in the MRI-scanner.

Blood glucose values should be maintained at values ranging from 5-10 mmol/l. Therefore, blood glucose values will be checked (and adjusted, if necessary, by the infusion of 5% glucose) before and after testing using a finger prick.

Imaging will be performed on a General Electric (GE) Signa 3T scanner using a phased-array head coil, with foam padding to restrict head motion. A localizer scan will first be performed for positioning of the image planes, followed by an automated shim procedure to improve magnetic field homogeneity.

[figure not shown]

#### *Structural MRI (sMRI)*

After either treatment period, the MRI session will end with a functional MRI and multi-sliced pulsed ASL (arterial spin labelling), to measure cerebral perfusion. To limit total acquisition time, and because brain structure is not expected to change over 12 weeks of treatment, the structural MRI sequences will be split and obtained on the two separate scanning days (at week 12 and at week 24). At week 12 (= after the first treatment period), the MRI-session will start with a 3D- T1- weighted MPRAGE (magnetization prepared rapid acquisition gradient echo). At week 24 (= after the second

treatment period), 3D-T2 and 3D-FLAIR (fluid attenuating inverse recovery), will be obtained, to identify white matter lesions.

### *Functional MRI (fMRI)*

During the fasting state, the effects of food-related and non-food-related stimuli on brain activation, and the effect of fasting on cognitive performance (memory), will be investigated, comparing both study insulins. Patients will be instructed about the scanning procedure, so they know what to expect. They will however not be aware of the food-related nature of the experiment prior to viewing of the stimuli in the scanner.

The fMRI will start with a resting state (RS) measurement. The following study design will be used [103-106]; in short, a series of food-related as well as non-food-related visual stimuli will be presented via a computer and back-projected onto a translucent screen, visible for the patients via a mirror. A two-button system will be applied to the patients' right hand. The volunteers will be asked to press the left button when the picture is taken "inside" or the right button when it is taken "outside"; this is to test the level of concentration, and to test whether this depends on the nature of the pictures (food-related versus non-food-related) that are shown. After this 'encoding' part of the experiment, ASL measurements will be made, which will take about 8 minutes. Then, a second series of pictures will be shown, using all pictures of the first series mixed with the same number of new pictures. The volunteers will be asked to press the left button when a new picture is seen or the right button when an old picture is recognised ('retrieval' part of the experiment). Correct answers will not be given.

### *Data analysis*

MRI data will be analysed using Statistical Parametric Mapping (SPM2) software, developed by the Wellcome Dept. of Cognitive Neurology, London, UK.

### *Summary MRI protocol (total scanning time: 44 min):*

1. 3D T1 weighted MPRAGE (week 12) OR  
3D FLAIR and 3D T2 to identify white matter changes (week 24)
2. fMRI resting state
3. fMRI encoding
4. Multi-slice pulsed ASL to measure cerebral perfusion
5. fMRI retrieval

| Treatment 12 w |                                                                                                | Treatment 12 w |                                                                                                     |
|----------------|------------------------------------------------------------------------------------------------|----------------|-----------------------------------------------------------------------------------------------------|
| Detemir        |                                                                                                | NPH            |                                                                                                     |
| NPH            |                                                                                                | Detemir        |                                                                                                     |
|                | MRI
T1

fMRI RS
fMRI encoding
ASL
fMRI retrieval
Total: 43' |                | MRI
FLAIR
T2
fMRI RS
fMRI encoding
ASL
fMRI retrieval
Total: 44' |

#### 5.4 Psychological assessment

The following questionnaires will be used:

- The Dutch version of the Eating Disorder Inventory (EDI-II) [107], to screen for eating disorders (visit 1).
- The Dutch version of the Center for Epidemiologic Studies Depression (CES-D) scale, one of the most widely used self-report instruments to measure current depressive symptomatology and to identify possible cases of depressive disorders [115-118] (visit 1).
- The Dutch Eating Behaviour Questionnaire [108-110]. This scale consists of 33 items and contains three scales for the measurement of emotional eating (overeating in response to emotions, 13 items), externally induced eating (eating in response to food related stimuli, regardless of the internal states of hunger and satiety, 10 items) and restrained eating (attempts to refrain from eating, 10 items) All items are rated on a five point scale ranging from 1 (seldom) to 5 (very often) and by dividing the total score by the number of valid answers, the overall score per type of eating behaviour can be calculated (range 1–5). Internal reliability coefficients (Cronbach's  $\alpha$ ) are 0,92 (0,93 in obese and 0,92 in non-obese) for the emotional eating scale, 0,80 (0,82 and 0,79 respectively) for the external eating scale and 0,93 (0,93 and 0,92 respectively) for the restraint scale in a sample of obese and non-obese men (45) (visit 2, 3, 5).
- 10-point Likert scale, to measure state of appetite, including hunger, fullness, desire to eat and prospective consumption [111, 112] (visit 3, 4, 5, 6).

- The Dutch version of the shortened Profile of Mood States (POMS) [113, 114], to assess current mood. The POMS is a self-report questionnaire consisting of 32 adjectives describing mood states which will be scored between 0 to 4. The described mood states are depression, anger, fatigue, vigor and tension (visit 3, 4, 5, 6).

## 6. STATISTICAL CONSIDERATIONS

### 6.1 General considerations

The null hypotheses will be tested at a two-sided level of 0.05. The null hypothesis *H0: No difference exists after a 12-week treatment with insulin detemir compared to NPH insulin with respect to the parameter of interest*. The null hypothesis will be tested against the hypothesis *H1: A difference exists after a 12-week treatment with insulin detemir compared to NPH insulin with respect to parameter of interest*. Last observation carried forward (LOCF) method will be used to impute missing data if necessary, however, baseline values will not be carried forward. A detailed statistical analysis plan will be produced prior to conduct of final data analysis.

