#### **Study design**

Randomised, open-label cross-over study. Type 1 diabetic patients will be treated on a basal-bolus regimen for two periods of 12 weeks, starting with insulin detemir or NPH insulin QD, administered in the evening, the prandial insulin being insulin aspart. PET and fMRI measurements and a lumbar puncture will be performed in the last week of both treatment periods.

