## **4. METHODS**

### **4.1. Study design**

A randomised, open-label cross-over study will be performed. This will allow to compare the results of two treatment regimens on the same group of patients, accounting for possible inter-individual differences in pharmacodynamics and –kinetics of the insulins used, by each individual being its own control. After a 4-week run-in period, during which patients continue their usual insulin, they will be treated for 12 weeks with either insulin detemir or NPH QD, administered in the evening, in combination with the prandial insulin analogue insulin aspart TID. A lumbar puncture, PET and fMRI measurements will be performed in the last week of this period, after which cross-over will take place and another 12 weeks of treatment, followed by the same procedures.

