#### 4.5. Study outline

[figure not shown]

The general study outline is presented in the figure above (a more detailed scheme is presented in Appendix 1). At visit 1, a voluntary, signed and dated informed consent will be obtained from the subjects prior to any trial related procedure. Participants will be screened for eligibility and enrolled into a run-in period of four weeks, during which they continue their usual insulin therapy. Further tests (Ewing test, assessment of DSP, fundoscopy) will be done, blood will be drawn (if this was not done at our hospital during the previous three months), insulin therapy will be reviewed, a detailed history will be taken and a physical examination will be done. At visit 2 blood will be drawn to measure HbA1c. Patients will be randomized to initial treatment with insulin detemir or NPH; this insulin is to be used once daily for the first 12 weeks, the prandial insulin will be the same during all study period for all participants (insulin aspart). Telephone contacts will be made during both treatment periods, to take a recent history, monitor adverse events and adjust insulin dose if necessary, which is of specific importance when the PET scan, MRI and LP will take place, at euglycaemic conditions.

In the last week of the first treatment period (visit 3), measurements will be performed at our institution to assess cerebral blood flow and glucose metabolism, by PET-scanning. In the same week, additional fMRI studies and a lumbar puncture will be performed (visit 4). At both visits, patients will have to fill out a short questionnaire concerning mood and feeling of satiety. Afterwards, patients will receive the new (the other) insulin, which is also to be used for 12 weeks, after which all procedures will be repeated (visit 5 and 6). At the end of the study period, patients can resume their previously used insulin; this will be discussed during the last visit.

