### 6.2 Analysis population

The intention to treat (ITT) population will consist of all subjects who took at least one dose of the randomized trial insulin beginning at the day of randomization. The evaluable population will consist of all ITT subjects who complete both 12-week treatment periods in compliance with the protocol.

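### For PET, fMRI and CSF, carrying the last observation forward can only fill a missing second period with the result under the other insulin, which pulls the treatment difference toward zero

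*Protocol*

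**What the plan says.** Section 6.1 of the protocol gives one missing-data rule for all outcomes: "Last observation carried forward (LOCF) method will be used to impute missing data if necessary, however, baseline values will not be carried forward". The same section fixes the test: "The null hypotheses will be tested at a two-sided level of 0.05".

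The design is a two-period cross-over (section 4.1: "A randomised, open-label cross-over study will be performed"). On timing, the study design paragraph of the protocol summary says "PET and fMRI measurements and a lumbar puncture will be performed in the last week of both treatment periods". Section 4.5 places the first PET session at visit 3 ("In the last week of the first treatment period (visit 3), measurements will be performed at our institution") and repeats the procedures at visits 5 and 6. The flow chart in Appendix 1 shows no PET, fMRI or lumbar puncture at visit 1 or 2.

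Section 6.2 defines two populations. "The intention to treat (ITT) population will consist of all subjects who took at least one dose of the randomized trial insulin", so no scan is needed to belong to it. The evaluable population is limited to patients who complete both periods in compliance with the protocol. The section does not say which population is primary. Section 6.4 allows for 25% drop-out among 40 patients.

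**The concern.** Last observation carried forward presupposes repeated measurements under one treatment. Here each imaging and CSF endpoint has one measurement per insulin. When the second is missing, the last observation is the week-12 result under the other insulin. Entering it at week 24 labels a detemir result as NPH, or the reverse, and that patient's difference is zero by construction.

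The bar on baseline values does not prevent this. The week-12 scan is an on-treatment endpoint, and the protocol nowhere calls it a baseline. A patient lost before the first scan has nothing to carry.

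The rule reaches both primary endpoints (CMRglu and CBF) and two secondary ones (CSF insulin and fMRI activity). Section 6.4 says the detemir-NPH difference on the primary endpoints has not been studied before. The size of that difference is therefore a main product of the trial, and it is what the rule would distort.

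**Working it through.** **Inputs.** From section 6.4: SD 10% (CMRglu) and 20% (CBF), 32 patients, 80% power, two-sided 5%, detectable differences 7.2% and 14.5%, 40 enrolled, 25% drop-out. The protocol does not say how many losses fall in period 2. The range used here is 2 to 10 of 40; 10 is 25% of 40, reached only if every loss comes after a completed first scan.

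**The plan's own figure.** Read the SD as within-patient, so the SD of a paired difference is s = SD × √2 = 14.14% for CMRglu and 28.28% for CBF. With 32 pairs, a paired t-test on 30 degrees of freedom has 80% power at 7.24% and 14.48%. Power at the stated 7.2% and 14.5% is 79.6% and 80.1%. The stated figures reproduce, so this reading of the SD is used below.

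**Effect of the imputation.** Let N be the patients analysed, f the share whose second value is a copy of the first, and d the true difference. Imputed patients contribute exactly 0. If drop-out is similar in the two sequences, or there is no period effect:

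- expected estimate = (1-f) × d
- standard error = √[(1-f)s² + f(1-f)d²] / √N
- standard error from observed pairs only = s / √[N(1-f)]

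Example for CMRglu with 8 of 40 imputed (f = 0.20, leaving the planned 32 pairs): the estimate is 0.80 × 7.2 = 5.76%. The standard error is √(0.80 × 200 + 0.16 × 51.84) / √40 = √168.29 / 6.325 = 2.05, against 14.14 / √32 = 2.50 from the observed pairs.

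CMRglu, true difference 7.2%, 40 analysed. Coverage is from 40,000 simulated period-adjusted cross-over trials per row, with losses balanced between sequences:

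| Imputed | Expected difference | SE, observed pairs | SE, LOCF | 95% CI half-width, observed pairs | Half-width, LOCF | Coverage, LOCF |
|---|---|---|---|---|---|---|
| 2 | 6.84% | 2.29 | 2.19 | 4.65 | 4.44 | 94.8% |
| 4 | 6.48% | 2.36 | 2.15 | 4.79 | 4.35 | 93.7% |
| 8 | 5.76% | 2.50 | 2.05 | 5.11 | 4.15 | 89.3% |
| 10 | 5.40% | 2.58 | 2.00 | 5.29 | 4.05 | 85.7% |

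Observed pairs alone keep coverage at about 95% in every row. For CBF with 8 imputed, 14.5% becomes 0.80 × 14.5 = 11.6%, with coverage 89.5%.

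If the 10 losses split evenly, the 5 lost in period 1 have nothing to carry and 5 of 35 are imputed. The expected estimate is 7.2 × 30/35 = 6.2%, with coverage about 93%.

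**Testing.** With 8 imputed, power is 79.3% under LOCF and 79.4% from observed pairs; with 10 it is 77.0% and 77.1%. Under no difference, the rejection rate stays between 4.8% and 5.1% under LOCF. Estimate and standard error shrink together, so the test hardly changes.

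**Where balance fails.** As an illustration only, assume a 5% shift between periods and all 8 losses in one sequence. With no true difference, LOCF then gives a mean difference of about 1.0% and a type I error of about 7.5%.

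**The case against.** The strongest reply is that the protocol never says a value crosses from one insulin to the other. It applies the rule only if needed, frames each comparison as after 12 weeks of treatment, and defers detail to a later analysis plan. Carry-forward within a period is a possible reading. That stands as a reading, but it does not rescue the rule: with one measurement per period it would impute nothing for PET, fMRI or CSF. The sentence is either wrong or empty for both primary endpoints, and a later plan would have to inherit it or contradict it.

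Second, the evaluable population largely avoids the problem, and enrolling 40 to obtain 32 suggests that drop-outs were not expected to supply pairs. Both observations are fair. But section 6.2 does not name the primary population, and its intention-to-treat set includes patients without a second scan.

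Third, a reader might infer two separate faults, a biased estimate and an understated standard error. The calculations do not support the second. With 10 imputed, the mean reported standard error is 1.99 and the actual spread of the estimates is 1.94. The interval is narrower than the observed pairs give, but it is honest about the spread of its own estimator. The undercoverage comes mainly from its shifted centre.

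Fourth, a reader might infer a loss of power or a raised false-positive rate. With balanced drop-out neither occurs; the 7.5% above depends on assumed imbalance together with an assumed period effect.

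Fifth, it is tempting to condemn carry-forward for every outcome. Weight, POMS and Likert are recorded at visits 3 and 4 and again at visits 5 and 6. Carrying within those pairs stays under one insulin.

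**Conclusion.** The point holds as a fault of estimation. For PET, fMRI and CSF, the rule in section 6.1 either replaces a missing second-period value with the other insulin's result or does nothing. In the first case the expected difference shrinks by the share imputed: for CMRglu, from 7.2% to between 6.8% and 5.4% with 2 to 10 of 40 imputed, and 95% coverage goes from about 95% to 86%.

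These figures rest on a true difference of 7.2%, a within-patient SD of 10%, 40 patients analysed, and drop-out similar in the two sequences or no period effect. The lower end, 5.4%, is a bound and not a forecast, because the protocol does not give the losses by period. Whether the trial would declare a difference is essentially unaffected when drop-out is balanced. The imputation therefore buys no power and costs accuracy in the reported effect.

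**What to change.** In section 6.1, state that no value is carried forward from one treatment period to the other. Analyse PET, fMRI and CSF endpoints on observed data with a linear mixed model (fixed treatment and period, random patient), which keeps patients with only one period without imputing the other. Report patients with both measurements as a sensitivity analysis. Carry-forward within a period (visit 3 to 4, visit 5 to 6) for weight, POMS and Likert need not be deleted.

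The cost is a short change to section 6.1 and matching text in the analysis plan, with no new data. The downside is that the intention-to-treat analysis no longer shows a value for every patient in both periods.

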### 6.2 Analysis population

The intention to treat (ITT) population will consist of all subjects who took at least one dose of the randomized trial insulin beginning at the day of randomization. The evaluable population will consist of all ITT subjects who complete both 12-week treatment periods in compliance with the protocol.

### 6.3 Primary study endpoints

As described before, the primary study endpoints of this study are:

- I. Cerebral metabolic rate of glucose ( $CMR_{glu}$ ) expressed as  $\mu\text{mol}/100\text{mg}/\text{min}$ , in brain regions associated with appetite regulation (e.g. amygdala, orbitofrontal cortex, insula, hypothalamus), as determined by FDG-PET scanning
- II. Cerebral blood flow (CBF), expressed as  $\text{ml}/100\text{mg}/\text{min}$ , in brain regions associated with appetite regulation (e.g. amygdala, orbitofrontal cortex, insula, hypothalamus), as determined by H2O-PET scanning

### 6.4 Justification of sample size

Sample size calculation is based on the primary endpoint, as determined by FDG- and H2O-PET. It is yet unknown whether any differences exist between insulin detemir and NPH insulin on these primary endpoints, since these have not been investigated before; therefore a minimal clinically relevant difference can only be estimated. No differential carry-over effect is expected [10, 119], so the study will be powered based on the cross-over design.

Based on the assumption that the standard deviation is 10% for  $CMR_{glu}$  and 20% for CBF - physiological and methodological variability (personal experience; [58, 97, 120, 121] )- a total of 32 patients will be needed in this crossover study. With this number of patients we are able (with a power of 80% and a two sided 5% significance level) to detect a difference of 7,2% in glucose consumption and 14,5% in perfusion between both treatment regimens. To account for a drop-out rate of 25%, a total of 40 patients will be included.

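### Forty patients do not cover the stated 25% drop-out: 30 would remain, not the 32 on which the 80% power rests

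*Protocol*

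**What the plan says.** Section 6.4 of the protocol sizes the trial on the two PET endpoints, as a cross-over ("so the study will be powered based on the cross-over design"). It assumes an SD of 10% for CMRglu ("Based on the assumption that the standard deviation is 10% for" CMRglu) and 20% for CBF ("and 20% for CBF - physiological and methodological variability"). It concludes that "a total of 32 patients will be needed in this crossover study". For that number it claims, "with a power of 80% and a two sided 5% significance level", the ability "to detect a difference of 7,2% in glucose consumption and 14,5% in perfusion between both treatment regimens". The allowance for losses comes last: "To account for a drop-out rate of 25%, a total of 40 patients will be included".

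Section 6.2 sets out who counts as evaluable: "The evaluable population will consist of all ITT subjects who complete both 12-week treatment periods in compliance with the protocol".

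**The concern.** An allowance for drop-out is meant to leave the required number of patients after the losses. Here it does not. A 25% loss from 40 leaves two patients fewer than section 6.4 itself requires. The required number, the drop-out rate and the enrolment are therefore inconsistent, and so is any reading in which 80% power at 7.2% and 14.5% survives a 25% loss.

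This paragraph is the whole case for the sample size, and it covers both primary endpoints. Anyone weighing the burden on patients (arterial cannulation and a lumbar puncture in each period) against what the trial can show would take from it a slightly better sensitivity than the plan supports under its own drop-out assumption.

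**Working it through.** **Inputs, all from section 6.4 unless noted**

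- Two-sided alpha 0.05, power 80%.
- SD 10% (CMRglu) and 20% (CBF).
- Detectable differences 7.2% and 14.5%.
- Required number 32, drop-out 25%, enrolment 40.
- Evaluable means completing both periods (section 6.2).
- One PET session per period, at weeks 12 and 24 (flow chart, Appendix 1).

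**Step 1: reproduce the protocol's base figure**

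The protocol does not say which SD it means. Taken as the SD of a single measurement, the SD of the within-patient difference is √2 x SD:

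- CMRglu: √2 x 10% = 14.14%
- CBF: √2 x 20% = 28.28%

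Power is that of a paired t-test, from the noncentral t distribution with noncentrality λ = δ√n / SD(difference), and n−1 or n−2 degrees of freedom (the latter if a period effect is fitted). At n = 32:

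- CMRglu: λ = 7.2 x √32 / 14.14 = 2.88; power 79.6–79.7%; difference detectable at 80% power 7.23–7.24%.
- CBF: λ = 14.5 x √32 / 28.28 = 2.90; power 80.1–80.2%; difference detectable at 80% power 14.46–14.48%.

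This gives the stated 7.2% and 14.5%. Other readings at n = 32 do not:

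| Reading at n = 32 | CMRglu | CBF |
|---|---|---|
| Protocol | 7.2% | 14.5% |
| Paired t, per-measurement SD | 7.23–7.24% | 14.46–14.48% |
| Normal approximation, per-measurement SD | 7.00% | 14.01% |
| Paired t, stated SD taken as SD of the difference | 5.1% | 10.2% |
| Parallel groups, 16 per arm (normal approximation) | 9.9% | 19.8% |

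**Step 2: the drop-out allowance**

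- Correct inflation: n / (1 − d) = 32 / 0.75 = 42.7, so 43 (44 for two equal sequences).
- What yields 40: n x (1 + d) = 32 x 1.25 = 40. The protocol shows no working, but this appears to be what was done.
- Remaining after 25% loss: 40 x 0.75 = 30.
- Loss that 40 does cover: 1 − 32/40 = 20%.

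**Step 3: what 30 completers deliver, by the method of step 1**

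| | CMRglu | CBF |
|---|---|---|
| λ at n = 30 | 7.2 x √30 / 14.14 = 2.79 | 14.5 x √30 / 28.28 = 2.81 |
| Power at the stated difference | 76.8–76.9% | 77.4–77.5% |
| Difference detectable at 80% power | about 7.5% | 14.97–14.99% |

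Like for like, going from 32 to 30 patients costs about 2.8 percentage points of power for each endpoint.

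**The case against.** The best case on the other side concerns size, and most of it stands.

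- **The loss is small and conditional.** Detectable differences move by 0.3 and 0.5 percentage points, and only if drop-out reaches 25%. At 20% or less, at least 32 patients remain and the stated figures are met; with no losses, 40 patients give about 88% power at the stated differences. All true.
- **The targets are not fixed relevance margins.** Section 6.4 concedes that a minimal relevant difference can only be estimated, and the SDs are round figures drawn partly from experience. The shift is small against that uncertainty. This bears on the consequence, not on whether the sentence is right.
- **The SD reading is inferred.** If 10% and 20% were SDs of the paired difference, power at n = 30 would be about 97%. But the stated differences would then not follow from 32 patients, and the shortfall of two patients would remain.
- **A normal approximation nearly removes the loss.** At n = 30 it gives 79.6% and 80.2% power (detectable 7.23% and 14.47%). The protocol, however, attaches 7.2% and 14.5% to 32 patients, where that approximation gives 7.00% and 14.01%.

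Three possible rescues fail:

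- Drop-out is not defined anywhere as a fraction of completers; eight lost out of 40 is 20%.
- No section provides for replacing drop-outs, and the enrolment is forty throughout.
- The last-observation-carried-forward rule in section 6.1 does not help. A patient who leaves before week 24 has no second-period scan, and carrying the first one forward would use a scan made on the other insulin, so it supplies no treatment contrast.

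**Conclusion.** The statement is wrong as written. Forty patients allow for a 20% drop-out, not 25%; at 25% the trial has 30 completers against a requirement of 32. This part is plain arithmetic, given that drop-out is counted as a share of those enrolled and is not replaced.

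If drop-out reaches 25%, the trial has 80% power for about 7.5% in CMRglu and 15.0% in CBF, and about 77% power at 7.2% and 14.5%. These figures rest on reading the stated SDs as per-measurement SDs and on a paired t-test, which together reproduce the protocol's own results. The practical effect is modest and does not call the design into question. The correction is still needed, because the figures in section 6.4 contradict one another.

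**What to change.** Keep 40 patients and correct the sentence in section 6.4 in one of two ways:

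1. State that enrolling 40 allows for a drop-out of 20%, leaving the required 32; or
2. Keep 25% and state that 30 evaluable patients give 80% power for differences of 7.5% in CMRglu and 15.0% in CBF (about 77% power for 7.2% and 14.5%).

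The choice should follow the drop-out the investigators actually expect. Under option 2, also say that the SDs are per measurement, so that the figures can be checked.

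The cost is one sentence and a slightly less favourable stated figure. No patients, visits or procedures are added. Raising enrolment to 43 would also resolve the conflict, but it would expose more patients to invasive procedures for about 3 points of power, and consistency does not require it.
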